### 5.1.b PARTICIPANT RETENTION

The IMPACT study plans to employ various methods in order to retain study participation.

#### **Reminders and Scheduling**

To ease some of the burden of the study participants, IMPACT staff members will contact study participants via telephone and/or email to remind them of their upcoming study appointments and to schedule their visit and exercise sessions. The schedules for study visits and exercise sessions will have a degree of flexibility to accommodate the study participants.

#### **Wellness Seminars and Newsletters**

While IMPACT is not offering monetary incentives, the study aims to offer incentives that promote positive health behaviors. IMPACT will develop and invite healthcare professors to provide wellness seminars specifically for study participants. IMPACT will also create monthly newsletters with health, nutrition, and wellness topics for study participants.

#### **Appreciation Events**

The IMPACT Study will hold appreciation events for its participants on an annual basis. These events provide the study participants an opportunity to learn about the progression of the study and also to meet and interact with study staff and other participants.

## 5.2 PARTICIPANT DISCONTINUATION

### 5.2.a PARTICIPANT DISCONTINUATION

The IMPACT study is based on voluntary participation. In other words, potential participants and study participants have the right to refuse participation and withdraw from the study at any time.

Circumstances may also arise where the study physician or nurse determines that a participant must withdraw from the study. Circumstances will be reviewed on an individual basis to determine if withdrawal from the study is to be temporary or permanent.

### 5.2.b CONTINGENCY PLAN FOR PARTICIPANT WELL-BEING

Study participants will be advised to seek medical care or advice from their usual healthcare provider for any conditions that may arise during the course of the study. If a participant is at a study visit when the medical condition occurs, the on-site study physician or study nurse will be notified immediately. IMPACT staff members are trained to recognize common life-threatening situations and can provide Basic Life Support (BLS) when necessary. If the medical condition is non-threatening but requires attention, the participant will be brought to SHC in its Fast Track program via the Emergency Department. If the medical condition is severe and life-threatening, IMPACT staff members will call 9-1-1 for emergency assistance. The IMPACT Study will send secure message via EpicCare to notify participant primary care provider (PCP) any medical occurrences.

## **Chapter 6: Randomization and Data Analysis Plan**

## 6.1 RANDOMIZATION

### 6.1.a RANDOMIZATION

Block Randomization is the method to be used to randomize study participants into study arms. The method is developed to pre-specify the number of arm assignments in a random order. IMPACT will utilize Block Randomization in conjunction with stratification in order to promote balance of participant characteristics within each study arm. The participant characteristics, or parameters, to be used for the IMPACT study includes: (1) age, (2) gender, and (3) HbA1c level.

Participant characteristics will be stratified as followed:

- Age (years)
  - >29.9 – 50.9 (young age)
  - 51.0 – 65.0 (older age)
- Gender
  - Male
  - Female
- HbA1c (percentage)
  - 6.6 – 7.9 (low A1c)
  - 8.00 – 9.9 (high A1c)

As a result, there are eight (8) strata in total:

1. Low HbA1c, younger age and female
2. Low HbA1c, younger age and male
3. Low HbA1c, older age and female
4. Low HbA1c, older age and male
5. High HbA1c, younger age and female
6. High HbA1c, younger age and male
7. High HbA1c, older age and female
8. High HbA1c, older age and male

Each block size will contain six (6) group assignments, evenly distributed across the three study arms. The blocks will contain random permutations (ie. 211332, 321231, etc) that are pre-determined by SAS.

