## **2.2 STUDY DESIGN**

### **2.2.a RANDOMIZED CONTROLLED TRIAL STUDY**

The IMPACT study will implement a three-arm randomized controlled trial (RCT). Of the three study arms, two will be experimental groups with structured exercise sessions (once-weekly or thrice-weekly) as the designed intervention. The remaining study arm will serve as the control group. The study randomization software will assign each eligible study participant into one of three study arms.

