### **Randomization**

Randomization is the process utilized to determine the study arm for each study participant. The specific randomization method to be used by IMPACT will be discussed in a later section. Once the study participant is ready to be randomized, his or her information will be inputted into the randomization software. Based on the provided information, the study participant will be assigned to the once-weekly experimental group (Arm 1), the thrice-weekly experimental group (Arm 2), or the usual care non-experimental group (Arm 3).

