#### **Randomization Envelopes**

IMPACT Biostatistician will prepare a total of eight (8) folders, one for each stratum. The specific group assignment within the folder will be included in six (6) sealed envelopes with the sequence within block on them.

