#### **Baseline Visit**

Randomization of study participants will take place during baseline visits. Once an individual has been officially enrolled into the IMPACT study, a staff member will review participant

characteristics and determine corresponding stratum. The participant will be given an envelope containing his or her study group assignment.

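### Fixed blocks of six in position-marked envelopes let up to about a fifth of assignments be deduced in advance, and other sections say software assigns the arm

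*Protocol*

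**What the plan says.** Section 6.1.a stratifies by age, gender and HbA1c, two levels each: "As a result, there are eight (8) strata in total". It fixes the block size: "Each block size will contain six (6) group assignments, evenly distributed across the three study arms". It also gives sample sequences: "The blocks will contain random permutations (ie. 211332, 321231, etc) that are pre-determined by SAS".

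Under Randomization Envelopes the list becomes paper: "IMPACT Biostatistician will prepare a total of eight (8) folders, one for each stratum". Then: "The specific group assignment within the folder will be included in six (6) sealed envelopes with the sequence within block on them". Under Baseline Visit in the same section, a staff member works out the stratum after enrollment, and "The participant will be given an envelope containing his or her study group assignment".

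Two other sections describe something different. Section 2.2.a: "The study randomization software will assign each eligible study participant into one of three study arms". Section 3.2.b (Randomization): once the participant is ready, "his or her information will be inputted into the randomization software", and the arm follows from what was entered.

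Two further parts of 3.2.b bear on this. A staff member makes the final eligibility decision from the checklist. After randomization, a staff member goes through the assigned arm with the participant.

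**The concern.** Concealment means that nobody deciding whether and when to enroll a person can tell what the next assignment will be. Three features of 6.1.a work against that. The block size is constant and printed in the protocol. The envelope shows the position within the block, so staff can see where a block begins and ends. Staff also learn every arm once it is assigned, since group exercise cannot be hidden from those who arrange it.

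Final eligibility under 2.4.c includes matters of judgement: willingness to attend, freedom from intervening events, and behavioral limits on participation. The schedule in 4.1.b places the final checklist and randomization at the same contact (R2). A person who expects a given arm next could delay or reconsider a borderline participant. Motivation and availability plausibly relate to adherence and HbA1c, so steering of that kind could bias the primary comparison, and adjustment for measured covariates would not reliably correct it.

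Separately, staff reading the protocol cannot tell whether software or an envelope decides the arm.

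**Working it through.** **Inputs.** Block of six, two per arm (6.1.a). Eight strata (6.1.a). 92 evaluable per arm and 20% attrition (6.2.b).

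**The plan's own figures.** 92 / (1 − 0.20) = 115 per arm; 115 × 3 = 345, as stated. 2 × 2 × 2 = 8 strata, as stated. Both sample sequences, 211332 and 321231, contain two of each arm. Expected recruitment per stratum is 345 / 8 ≈ 43, or about 43 / 6 ≈ 7.2 blocks.

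**Predictability in one block.** There are 6! / (2! × 2! × 2!) = 90 equally likely sequences. For an observer who knows the block size and all earlier assignments in the stratum:

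| Position | Next arm certain | At least one arm ruled out | Best-guess accuracy |
|---|---|---|---|
| 1 | 0 | 0 | 0.333 |
| 2 | 0 | 0 | 0.400 |
| 3 | 0 | 0.20 | 0.500 |
| 4 | 0 | 0.60 | 0.533 |
| 5 | 0.20 | 1.00 | 0.600 |
| 6 | 1.00 | 1.00 | 1.000 |
| Mean | 0.200 | 0.467 | 0.561 |

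Derivation of the less obvious entries:
- Position 5, certain: the two remaining assignments are the same arm with probability 3/15 = 0.20.
- Position 3, one arm ruled out: the first two match with probability 3/15 = 0.20.
- Position 4, one arm ruled out: the first three are not all different, 1 − 8/20 = 0.60.
- Means: 1.2/6 = 0.200 and 2.8/6 = 0.467.

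Whether the next assignment is usual care or not is settled for (1/15 + 3/15 + 7/15 + 15/15) / 6 = 0.289 of assignments. Chance accuracy is 0.333.

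**Applied to 345.** With complete blocks, 0.20 × 345 = 69 assignments are certain. Simulating 345 participants over eight equally likely strata, with incomplete last blocks, gives 18.9% certain (about 65), 45.0% with an arm ruled out, and best-guess accuracy 0.553. One unequal stratum mix gave the same count, about 65.

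**With varying block sizes.** The observer knows the set of sizes, each equally likely, but not the size of any given block:

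| Block sizes | Certain | Arm ruled out | Best guess |
|---|---|---|---|
| 6 only | 18.9% (about 65) | 45.0% | 0.553 |
| 3/6/9 | 3.6% (about 13) | 10.4% | 0.547 |
| 6/9/12 | 2.3% (about 8) | 6.7% | 0.520 |

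Varying the size removes most of the certainty and little of the guessing advantage.

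**The two mechanisms.** Generating permutations in SAS is compatible with envelopes, so that sentence in 6.1.a is not itself the conflict. The conflict is between 2.2.a and 3.2.b, where software assigns the participant at the time of randomization, and the envelope text in 6.1.a.

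**The case against.** The plan has real safeguards. The envelopes are sealed and prepared by the biostatistician. Section 3.2.b orders the steps as eligibility review, enrollment, randomization, and 6.1.a hands over the envelope only after enrollment. This protects the individual envelope and stands. It does not prevent someone from counting what is left in a block before judging the next candidate.

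The figures assume an observer who tracks all eight strata without error, and no assignment is certain before position five. That also stands, so the figures are ceilings. Section 3.2.b defers the method to a later section, which suggests that 6.1.a governs. However, 2.2.a carries no such deferral and 3.2.b still describes data entry into software, so the text needs reconciling either way.

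A reader might infer three stronger things that the document does not support.
- That one person both decides eligibility and hands over the envelope. The protocol speaks only of a staff member in each place, and the handover is in the passive. The visible text states no separation of roles. Section 7.1.a on the study team was not in the text available, so a separation there cannot be excluded.
- That the envelopes run out, since 8 × 6 = 48 is far below 345. Section 6.1.a speaks of blocks in the plural and of position within a block, so the natural reading is one block per folder at a time, with more to follow. The resupply is not described, but no shortage is planned.
- That selection bias is established. The arithmetic shows the opportunity. It estimates no effect on HbA1c.

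**Conclusion.** The point holds as a concealment weakness together with an internal contradiction. Followed as written, the envelope procedure would let a person tracking assignments know up to 20% of them with certainty (about 19%, or 65 of 345, with incomplete blocks) and exclude at least one arm for about 45% to 47%.

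This rests on three assumptions: that staff are aware of each arm, which follows from their explaining it to participants although the protocol does not use the word unblinded; that someone involved in eligibility keeps or recalls earlier assignments by stratum; and that envelopes rather than software are used. If software is used, the exposure from visible positions disappears, but the fixed block size remains and the envelope text is wrong. The contradiction needs correcting whichever route is meant. Because the change is cheap and bears on the primary comparison, it should be made.

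**What to change.** 1. Reconcile 2.2.a, 3.2.b (Randomization) and 6.1.a (Randomization Envelopes, Baseline Visit) to one concealed mechanism. Electronic or central allocation is preferable, releasing the arm only after enrollment is recorded. This is the main repair.
2. Generate the stratified list with randomly varying block sizes, for example 3/6/9 or 6/9/12, and keep the sizes out of documents that enrolling staff use.
3. If envelopes are kept, number them consecutively within stratum, leave off the position within block, and state how further blocks are supplied without showing where one ends.
4. State who judges final eligibility and who handles allocation.

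The cost is a regenerated list, some set-up effort, and a slightly larger possible arm imbalance within strata. Section 9.2.a describes REDCap only for storing and managing data and for surveys, so whether it can also serve for allocation has to be confirmed first.

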#### **Randomization Envelopes**

IMPACT Biostatistician will prepare a total of eight (8) folders, one for each stratum. The specific group assignment within the folder will be included in six (6) sealed envelopes with the sequence within block on them.

#### **Baseline Visit**

Randomization of study participants will take place during baseline visits. Once an individual has been officially enrolled into the IMPACT study, a staff member will review participant

characteristics and determine corresponding stratum. The participant will be given an envelope containing his or her study group assignment.

## **6.2 DATA ANALYTICAL METHODS**

### **6.2.a DATA ANALYSIS PLAN**

Statistical analyses will investigate clinical effectiveness of structured physical activity regimens across varying frequencies. The main statistical approach will be to date-match outcomes to concomitant exercise regimens, then to examine univariate and multivariate associations with changes in clinical outcomes, patient-centered outcomes, and cost. Statistical significance will be determined at  $P < 0.01$ , a stricter value due to the expected number of models used, or with other adjustments for multiple comparisons when applicable. Statistical analyses will be performed using SAS® (Cary, NC), and supplemented with STATA or Splus for methods not available in SAS®.

Study participants who are not able or willing to continue with the randomized frequency of intervention will be treated as loss to follow-up and only data obtained while in the assigned protocol will be used in the primary analysis (intention-to-treat). Since participants and non-participants continue to receive care within the healthcare system contemporaneously during the research study, IMPACT will obtain interstitial outcome data and complete clinical narrative through observational data available in the EHR. The statistical analysis will be conducted by Senior Statistician/s with the guidance of Biostatistical Consultant [name].

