### **Statistical Analysis**

In univariate analyses, the percent change from baseline will be compared across intervention arms using appropriate parametric (ANOVA, *t* tests) or non-parametric (Wilcoxon) methods.

In multivariate analyses, change in outcomes will be modeled using linear regression. Percent change from baseline will be a continuous outcome with intervention arm as the predictor of interest and various participant characteristics as covariates (e.g. sex, age, race/ethnicity, anthropometry, self-reported diet and exercise, pharmacotherapy, family history, etc.). Repeated measures analysis using the outcome at different time points and mixed-effects models will also be performed. Available nonparticipants will serve as contemporaneous comparators to address possible secular trends in outcome values.

Study participants in the exercise program may also be undergoing concomitant pharmaceutical therapy to reduce HbA1c. The approach is to repeat the above analyses stratified by use of hypoglycemic medication. Another approach is to use a composite binary outcome variable for whether participants were successful in either decreasing diabetes medication or reduced HbA1c by 0.5% without increasing medications. Logistic regression will be used to assess the likelihood of achieving the composite outcome.

Study participants will be studied based on their randomized assignment (intention-to-treat). In sensitivity analyses, participants may be re-analyzed based on actualized attendance if they more closely resemble one of the other arms (once-weekly, thrice-weekly, usual care). A study participant assigned to thrice-weekly, who attends only once a week may be re-analyzed as a weekly patient. Stratification by adherent (attendance >80%) or not will also be another sensitivity analysis.

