## 8.3 STUDY DISCONTINUATION

### 8.3.a EARLY DISCONTINUATION OF TREATMENT

If a study participant is removed from the study prior to completion of the intervention, the reason and date will be documented. If a study participant is removed from the study, the follow-up assessments will be obtained. If the study participant is removed because of intolerance or complications related to the intervention, the study participant would remain under medical observation until resolution or stabilization of the adverse event. Participants will be removed from the study for any of the following reasons:

- The study participant has a serious or life-threatening adverse event.
- The study participant develops serious illness.
- The study participant becomes pregnant during the study term.
- The study participant begins insulin therapy.
- The study participant enrolls in a clinical trial which interferes with study procedures and outcomes.
- The study participant suffers physical injury preventing the continuation of study intervention.
- The investigator feels that it is in the best interest of the study participant to withdraw.
- The study participant wishes to withdraw.
- The study participant fails to comply with the intervention protocol, assessments, or other requirements of the study.

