#### Secondary Data Sources

Secondary data sources are existing datasets collected by another entity. The IMPACT Study will use EpicCare EHR to obtain HbA1c results and other metabolic measurements if participants do not attend their study visits.

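### The primary analysis labelled intention-to-treat omits HbA1c measured after a participant stops the assigned exercise frequency, and this conflicts with the Aim 1 text on analysis as randomised

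*Protocol*

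**What the plan says.** The general text of Protocol section 6.2.a (Data Analysis Plan) takes two steps. First, "Study participants who are not able or willing to continue with the randomized frequency of intervention will be treated as loss to follow-up". Second, "only data obtained while in the assigned protocol will be used in the primary analysis (intention-to-treat"). The same section describes its overall method this way: "The main statistical approach will be to date-match outcomes to concomitant exercise regimens".

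Further on in 6.2.a, the Statistical Analysis text for Study Aim 1 states: "Study participants will be studied based on their randomized assignment (intention-to-treat"). It then adds: "In sensitivity analyses, participants may be re-analyzed based on actualized attendance". Splitting participants by attendance above 80% is also called a sensitivity analysis there. Yet the Aim 1 paragraph on primary outcomes and process measures makes adherence a covariate for stratification or adjustment, without limiting it to sensitivity analyses.

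Two other sections bear on the data that would be left out. Section 8.3.a lists grounds for removal, one of them being: "The study participant fails to comply with the intervention protocol, assessments, or other requirements of the study". It also says: "If a study participant is removed from the study, the follow-up assessments will be obtained". Section 9.1.a, under Secondary Data Sources, says: "The IMPACT Study will use EpicCare EHR to obtain HbA1c results and other metabolic measurements if participants do not attend their study visits".

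**The concern.** Whether a participant keeps up the assigned frequency is known only after randomisation, and it may well be related to glycaemic control. If outcome data are kept or left out on that basis, the arms being compared are no longer those that randomisation made comparable.

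The rule is also lopsided. Usual care (Arm 3) attends study visits only and has no exercise frequency to give up, so this form of censoring falls mainly on Arms 1 and 2. It can bias exercise against usual care. If stopping differs between one and three sessions a week, it can also bias the comparison of the two exercise arms.

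The trial's stated purpose (section 1.1.a) is to find a contact frequency that is feasible as well as optimal in a clinic. Outcomes in people who could not sustain a frequency are part of that answer, and the rule takes them out of the primary result.

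**Working it through.** **1. The texts side by side**

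| Question | 6.2.a, general text | 6.2.a, Aim 1 | 8.3.a and 9.1.a |
|---|---|---|---|
| Which arm is a participant counted in? | Randomised arm, by the label used | Randomised arm | not addressed |
| Is HbA1c before stopping used? | Yes | Yes | not addressed |
| Is HbA1c after stopping used? | No | Not said; the restriction is not withdrawn | Planned to be collected after removal, with EHR values for missed visits |
| Where do attendance and adherence enter? | Matching to the concurrent regimen is the main approach | Covariate in one paragraph, sensitivity analysis in another | Non-compliance is a ground for removal |

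An analyst could follow either part of 6.2.a and claim to comply, and the two can give different primary results. Section 6.2.b does not settle it: the multiple imputation there is for missing covariates, so it does not restore the omitted outcomes.

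**2. The protocol's own figure**

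Section 6.2.b: 92 evaluable per arm with 20% attrition gives 92 / (1 − 0.20) = 115 per arm, and 3 × 115 = 345. This reproduces. The 92 cannot be derived independently, because no SD is stated. Inverting the two-sample formula at two-sided alpha 0.05/3 (two-sided is assumed) and 80% power:

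SD = 0.5 / [(2.394 + 0.842) × √(2/92)] = 0.5 / (3.236 × 0.1474) ≈ 1.05 points.

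**3. Illustration of size, under no true effect**

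Assumed, because the documents give none of these: the SD; the share p of an exercise arm that stops; and the amount g by which stoppers' HbA1c is worse than that of those who continue. It is also assumed that values before stopping recover nothing, and that no usual-care data are censored. Then:

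- Bias in favour of exercise = p × g. For p = 20% and g = 0.5, this is 0.20 × 0.5 = 0.10 point.
- Standard error = SD × √(2/92). At SD 1.0 it is 0.147.
- Type I error = P(|Z + bias/SE| > 2.394). Here bias/SE = 0.10/0.147 = 0.68.

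| Bias 0.10 point, 92 per arm | Type I error |
|---|---|
| SD 0.8, alpha 0.0167 | 0.062 |
| SD 1.0, alpha 0.0167 | 0.044 |
| SD 1.5, alpha 0.0167 | 0.028 |
| SD 1.0, alpha 0.01 (critical value 2.576) | 0.029 |

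The last row is there because section 6.2.a sets significance at P < 0.01, whereas section 6.2.b uses 0.05/3. Each result is above its nominal level.

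**4. Power if stoppers' later data are kept**

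Assumed: SD 1.05, all 115 per arm analysed, two-sided alpha 0.0167. SE = 1.05 × √(2/115) = 0.1385.

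- Full 0.5-point effect: 0.5/0.1385 = 3.61, power about 0.89.
- 20% of the exercise arm stop and gain nothing: effect 0.8 × 0.5 = 0.40, 0.40/0.1385 = 2.89, power about 0.69 (0.74 at SD 1.0, 0.55 at SD 1.2).

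**The case against.** The strongest reply is that the Aim 1 text is the more specific one. It covers the primary outcome, analyses participants as randomised and confines attendance-based regrouping to sensitivity analyses. It also plans repeated-measures and mixed-effects models, which can use values from before stopping. Some secondary hypotheses in section 2.3.b are worded around participants who adhered or maintained their schedule, so an on-treatment question is not foreign to the trial. This stands in part: the protocol contradicts itself rather than settling on an on-treatment analysis. But the Aim 1 text never lifts the data restriction, the primary hypothesis in section 2.3.a compares the interventions with usual care, and adherer questions fit the sensitivity analyses already listed.

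A reader might infer more than the documents support:

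- **That stoppers are deleted, so motivated exercisers are compared with all controls.** The rule censors later data; earlier values stay in the randomised arm. For a given p and g, p × g is therefore closer to an upper case.
- **That participants who start insulin are excluded, removing glycaemic failures from the exercise arms.** Starting insulin is a removal ground in 8.3.a, in any arm, and follow-up is planned after removal. Nothing says those data are excluded. If they were, losing failing controls would bias against exercise.
- **That almost all exclusions fall in the exercise arms, most of them in the thrice-weekly arm.** The first is too strong and the second is plausible, but no figure supports either.
- **That the omitted HbA1c values are certain to exist.** They are planned, but 8.3.a also covers participants who wish to withdraw, and EHR values depend on routine care and need not match visit dates or the study's point-of-care test.

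**Conclusion.** The point holds. The primary-analysis rule in section 6.2.a is on-treatment censoring under an intention-to-treat label, and it conflicts with the Aim 1 text of the same section. It leaves out HbA1c after stopping that sections 8.3.a and 9.1.a plan to obtain. Because the choice decides the primary result, it should be settled before analysis.

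That conclusion rests on the wording alone. The size does not: the SD, the share stopping and their deficit are all assumed. Under those assumptions a 0.10-point bias, one fifth of the 0.5-point target, lifts the type I error from 0.0167 to between 0.028 and 0.062 for SDs from 1.5 down to 0.8. The direction for exercise against usual care follows only if stoppers do worse than continuers. A bias between the two exercise arms requires that stopping differ between them.

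**What to change.** Replace the restriction in 6.2.a with wording such as: *The primary analysis includes every randomised participant in the assigned arm and uses all HbA1c values collected for the scheduled time points, whether or not the participant kept to the assigned sessions or was removed under 8.3.a. EHR values are used for missed visits as set out in 9.1.a. Missing outcomes are handled by a likelihood-based repeated-measures model or by multiple imputation.*

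Then bring the rest into line:

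- Move the matching of outcomes to concurrent exercise regimens, the adjustment or stratification for adherence, and the on-protocol analysis to labelled secondary or sensitivity analyses.
- Reconcile the general text of 6.2.a, both Aim 1 paragraphs and 8.3.a on how data after stopping or removal are used. This concerns the analysis only; no removal rule needs to change.

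The cost is not only wording. No new data collection is needed, but retained stoppers may dilute the effect, and the 20% attrition allowance in 6.2.b was not set for that. The sponsor should acknowledge the possible fall in power, illustrated above as about 0.89 to about 0.69.
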